### Sample Size

The sample size for the trial was calculated using the following formula for estimating the difference between 2 proportions [22]. A 5% α error was allowed, and 80% power was expected when calculating the sample size. A 50% increase in the factor of interest was assumed, as a meta-analysis on behavioral modifications showed an increase in factors of interest by 50%. As the 2015 STEPS survey reported that only 28% of the population had met the recommended number of fruit and vegetable servings [5], 0.3 was assumed as the baseline proportion for the recommended fruit and vegetable intake and was expected to increase by 50% at the end of the intervention. Therefore, 0.45 was assumed as the proportion in the intervention arm after the intervention.

Substituting the aforementioned values in the equation, the calculated minimum sample size in each arm of the cluster randomized trial was 160.

Design effect for cluster sampling was calculated assuming a cluster size of 30 and an intraclass correlation of 0.02 because the intraclass correlation coefficient in human studies usually lies between 0.01 and 0.02. A study among office workers reported an intraclass correlation coefficient of 0.02 [23]. Substituting the aforementioned values in the equation, the design effect for this study was 1.58.

Therefore, the minimum sample size for each arm was 253. After accounting for a 10% dropout rate, the study’s minimum sample size per arm was 280 office workers. Thus, the minimum sample size in the intervention and control groups was 560 office workers.

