### Randomization

After baseline data collection, all selected clusters were randomized into 2 arms. The principal investigator or data collectors did not know whether a particular cluster belonged to the control or intervention arm at baseline data collection, which minimized observer bias during this stage.

All selected clusters were arranged in ascending alphabetical order, and a number was assigned to each cluster. An online randomization sequence generator assigned the numbers 1 to 20 into 2 arms. The intervention arm had 10 numbers, and the control arm had 10 numbers. Clusters with allocated numbers were randomly assigned to the intervention and control arms.

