### Data Analysis

The distribution of basic sociodemographic characteristics, NCD status, dietary behaviors and practices, and work-related characteristics of the participants in the intervention and control arms will be assessed to determine whether the 2 groups were comparable at baseline.

Bivariate and multivariate analyses will be used to assess the effectiveness of the intervention. Progressive improvement in the SOC will be used as the primary outcome. Those who underwent a progressive change in their SOC will be coded as 1, and those who did not undergo such a change will be coded as 0. Similarly, those who changed from an unhealthy to a healthy diet or persisted in a healthy diet will be coded as 1, and those who did not will be coded as 0. Furthermore, changes in the intake of individual food groups to recommended levels will be coded as 1 and 0 similarly.

Bivariate analysis will use the primary and secondary outcomes as the dependent variables and sociodemographic factors, NCD status, dietary behaviors, and social relations as the independent variables. The chi-square test, independent-sample *t* test (2-tailed), and Mann-Whitney *U* test will be used as appropriate. Multivariate analysis will be conducted using binary logistic regression with the forward selection option to build the model. The variables included in the model will be determined based on demonstrating significant associations with the outcome variables in the bivariate analysis.

Sociodemographic factors, NCD status, dietary behaviors, social relations, and the allocated arm of the participants lost to follow-up will be compared with those of other participants to ensure no selective data loss. Further analysis will be conducted separately under two assumptions as follows: (1) all participants lost to follow-up achieved the primary and secondary outcomes, and (2) all participants lost to follow-up did not achieve the primary and secondary outcomes.

Odds ratios will be reported for the 2 assumptions separately. The level of probability will be set at .05 for all analyses.

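### Offices were randomised and the sample size was inflated for clustering, but the named tests treat workers as independent; a simple arm comparison at .05 then carries about 7.5% to 12% type I error over the protocol's own ICC range

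*Protocol article*

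**What the plan says.** The unit of randomisation is the office. The Randomization section states: "After baseline data collection, all selected clusters were randomized into 2 arms". On the split it adds: "The intervention arm had 10 numbers, and the control arm had 10 numbers".

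The Sample Size section accepts that workers in one office are correlated: "Design effect for cluster sampling was calculated assuming a cluster size of 30 and an intraclass correlation of 0.02". The resulting design effect of 1.58 takes 160 workers per arm to 253, and an allowance for dropout takes that to 280.

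The Data Analysis section scores each worker 1 or 0 on the primary outcome (progression in stage of change) and likewise on the secondary and food-group outcomes. It names the chi-square, independent-sample t and Mann-Whitney U tests for the bivariate step. For the model it says: "Multivariate analysis will be conducted using binary logistic regression with the forward selection option to build the model". The threshold is fixed: "The level of probability will be set at .05 for all analyses". Two further analyses assign an outcome to everyone lost to follow-up.

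No section mentions a random office effect, GEE, cluster-robust variance, an office-level summary or a design-effect correction to the tests. The Discussion warns that randomising clusters leaves room for other influences, but that is a caution about interpretation and not a method.

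**The concern.** The design and the sample size treat the office as the unit that carries the randomisation; the named analysis treats the worker as that unit. If workers in an office resemble one another, the arm comparison holds less information than the number of workers suggests. A test that ignores this uses too small a standard error, gives confidence intervals that are too narrow, and rejects a true null hypothesis more often than 5% of the time. A positive result could then reflect ordinary differences between offices. The same fault would carry into the secondary and food-group outcomes and the odds ratios under both loss-to-follow-up assumptions. The article expects the results to inform local policy.

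**Working it through.** **Inputs.** From Sample Size: proportions 0.30 and 0.45, 5% alpha, 80% power, cluster size 30, ICC 0.02 with a stated usual range of 0.01 to 0.02. From Randomization: 10 offices per arm. From Results: 518 workers recruited and 439 assessed after the intervention (220 and 219). Two-sided testing is assumed, because it reproduces the stated sample size.

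**Step 1: reproduce the plan's figures.**
- Per arm before clustering, unpooled variance: (1.96 + 0.8416)² × (0.30×0.70 + 0.45×0.55) / 0.15² = 7.849 × 0.4575 / 0.0225 = 159.6, so 160.
- Design effect: DE = 1 + (30 − 1) × 0.02 = 1.58.
- 160 × 1.58 = 252.8, so 253.
- Dropout of 10%: 253/0.9 gives 282 and 253 × 1.1 gives 279; the stated 280 lies between them.

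The sample size therefore does allow for clustering, and the arithmetic is sound.

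**Step 2: error rate of a test that ignores clustering.** With DE = 1 + (m − 1) × ICC, where m is the number of workers per office, the naive standard error is too small by a factor √DE. The true two-sided error at nominal 5% is 2 × [1 − Φ(1.96/√DE)].

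| Workers per office (m) | ICC | DE | True type I error |
|---|---|---|---|
| 439/20 = 21.95 (assessed) | 0.02 | 1 + 20.95×0.02 = 1.419 | 10.0% |
| 518/20 = 25.9 (loss-to-follow-up scenarios) | 0.02 | 1 + 24.9×0.02 = 1.498 | 10.9% |
| 30 (design) | 0.02 | 1.58 | 11.9% |
| 21.95 | 0.01 | 1.21 | 7.5% |
| 30 | 0.01 | 1.29 | 8.4% |

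The protocol's own inputs therefore give about 7.5% to 12%.

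**Step 3: check by simulation.** Beta-binomial data with 10 offices per arm, outcome proportions of 0.30 and 0.45, and 200,000 runs per setting, at ICC 0.02 and 22 workers per office:
- chi-square without continuity correction: 9.9% to 10.3%;
- Wald test from logistic regression on arm: 9.9% to 10.1%;
- chi-square with Yates correction: 8.2% to 8.7%.

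A t test on the 20 office proportions (18 df) held 4.9% to 5.1% in every setting.

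**Step 4: interval width.** At ICC 0.02 and 21.95 per office, √1.419 = 1.19. A t reference on 18 df adds a factor 2.10/1.96 = 1.07. Together, 1.19 × 2.10/1.96 = 1.28, so a correct interval is about 28% wider than the naive one.

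**Sensitivity beyond the protocol.** At about 22 per office, the error would be about 17% at ICC 0.05 and about 26% at ICC 0.10. Both ICC values are assumptions of this review, not figures from the protocol.

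**The case against.** **A fuller analysis plan may handle clustering.** The article is condensed, and logistic regression can be run with a cluster-robust variance. It would be fair to leave silence on such detail to a statistical analysis plan. The article is not silent, however: it names specific tests, a model and a selection rule, and in standard form these conflict with its own design effect. What stands is that the article nowhere says clustering will be ignored. The finding is about the methods as written.

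**The 10% is conditional.** A reader might infer that the primary test is known to run at 10%. The documents do not support that. The ICC of 0.02 comes from another study of office workers and enters a calculation about fruit and vegetable intake; no ICC is given for progression in stage of change. A reader might also take 17% or 26% as the likely size, but these need ICCs outside the stated range. This objection stands and is why a range is reported.

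**The figure is not for the whole planned procedure.** The plan screens variables by bivariate significance and then applies forward selection. Study arm is not listed among the bivariate independent variables, so the primary test of arm is not clearly defined. The error rate of the full screen-and-select procedure was not computed. The figures apply to a simple arm comparison, by chi-square or logistic Wald test. This also stands, but it gives no reason to expect that the full procedure would correct for clustering.

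**Conclusion.** The inconsistency is real and should be resolved before the effectiveness analysis. Offices were randomised and clustering was accepted in the sample size, yet the named tests assume independent workers. For a simple arm comparison at nominal .05, the true type I error is about 10% at ICC 0.02 and about 22 assessed workers per office. It is about 10.9% in the two loss-to-follow-up scenarios if the same ICC applies there, and about 7.5% to 12% over ICC 0.01 to 0.02 and 22 to 30 workers per office.

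These values assume offices of equal or nearly equal size and an ICC for stage-of-change progression like the one used for the sample size. The exact size is uncertain but the direction is not: without continuity correction, the error exceeds 5% at any positive ICC.

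**What to change.** Before the analysis is run, name **one** primary method for the arm effect that respects offices and suits 20 clusters. An example is GEE logistic regression with exchangeable correlation by office, a small-sample variance correction and a t reference on about 18 df (20 offices minus 2). Naming one matters because GEE and a random-intercept model estimate different odds ratios, and an open choice after data collection could be settled by the results. Date the decision and declare it as a change made after data collection.

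In addition:
- run a t test on the 20 office proportions as a check;
- report the observed ICC for the primary outcome;
- apply the same method to the secondary and food-group outcomes and to both loss-to-follow-up scenarios.

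**Cost.** The change is to the analysis wording, and the Results section says the effectiveness analysis was still to be completed. No new data should be needed: workers were sampled, assessed and allocated office by office. The article mentions only a serial number as identifier, so it should be confirmed that each record can be linked to its office. At ICC 0.02, intervals will be about 28% wider than under the named methods, which is the correct width.

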### Participant Timeline

Data from a cross-sectional study were extracted for all selected government offices in the Galle district, and 2 months were allocated for this. Data on participants’ demographic profiles, health conditions, dietary practices, SOC, and dietary intake were extracted from the aforementioned cross-sectional study as preintervention or baseline data for the interventional study. Randomization was conducted following the baseline data collection. Once randomization was done, the principal investigator and resource person for lectures visited each office in the intervention arm on a prescheduled day. All participants in the study were informed of the date beforehand. The principal investigator applied the intervention, and the resource person delivered lectures. If any participant missed the initial intervention, a second visit was arranged to achieve maximum participation. The initiation of the intervention in all 10 selected offices was completed within 1 month. Monthly assessments and lectures were conducted on prescheduled days following one, two and three months of the initiation date for each office. However, a second day was not arranged for monthly assessments and lectures. A postintervention assessment was conducted at the end of 3 months. The date for the postintervention evaluation was given to all participants to ensure that they took part in the assessment. If any participant missed the postintervention assessment, another day was arranged. Figure 1 shows the flow of participants through the intervention process.

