#### Primary Outcome

The primary outcome of the intervention was a progressive change in the SOC, which was defined as *progression from a lower SOC to a higher SOC*.

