**Figure 2 figure2:**
[figure not shown]
CONSORT (Consolidated Standards of Reporting Trials) flow diagram for a stage of change theory–based, stage-matched intervention for healthy dietary intake among office workers. *The intervention group was divided into 2 groups depending on the participants’ stage of change at the beginning. Two different interventions were implemented for each group. One group included 143 participants at the beginning and 127 participants at the end, and the other included 123 participants at the beginning and 97 participants at the end. **Postintervention analysis has not yet been completed.

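### The check for selective loss to follow-up omits baseline stage of change and describes no lost-versus-retained comparison within arm, so it could miss loss that differs by stage

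*Protocol article*

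**What the plan says.** The Data Analysis section names the variables, the comparison group and the purpose of the check. The variables are: "Sociodemographic factors, NCD status, dietary behaviors, social relations, and the allocated arm of the participants lost to follow-up will be compared". The comparison group and purpose stand in the same sentence: "the allocated arm of the participants lost to follow-up will be compared with those of other participants to ensure no selective data loss". Stage of change is not named.

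The same paragraph then plans two further analyses, one counting every lost participant as having achieved the outcomes and one counting every lost participant as not having achieved them, with odds ratios reported for each. The significance level is .05 for all analyses.

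Participant Timeline shows that stage is available at baseline and is a variable in its own right: "Data on participants’ demographic profiles, health conditions, dietary practices, SOC, and dietary intake were extracted" from the earlier cross-sectional study. Under Primary Outcome: "The primary outcome of the intervention was a progressive change in the SOC". The Figure 2 caption states that "The intervention group was divided into 2 groups depending on the participants’ stage of change at the beginning", with a different intervention for each, and gives the counts: "One group included 143 participants at the beginning and 127 participants at the end, and the other included 123 participants at the beginning and 97" at the end.

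**The concern.** A check of this kind is useful only if it looks at the characteristics most likely to link loss with outcome. Here that is baseline stage. It determines whether a participant gets the lectures or the serving counter, and progression is measured from it. It also limits the outcome: a participant already in maintenance has no higher stage to reach and can only be coded 0.

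The second gap is the form of the comparison. All lost participants are set against all others, and arm appears as one more characteristic. That shows whether one arm lost more people. It does not show whether the two arms lost different kinds of people, which is the pattern that can bias the arm comparison.

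At stake is the statement that the check is meant to support. It could read as reassurance about the 439 participants with postintervention data when the variable most relevant to the primary outcome was never examined.

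**Working it through.** **Inputs.** Results section: 266 intervention and 252 control participants at baseline; 220 and 219 at the end. Figure 2 caption: 143 to 127 and 123 to 97 in the two intervention stage groups. Data Analysis: level .05. The article names no test for this check, so an ordinary chi-square test is assumed.

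**1. Reproduce the counts.** Baseline: 143 + 123 = 266, which agrees with the text. End: 127 + 97 = 224, against 220 in the text. Four participants are unreconciled.

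**2. Loss by stage group, caption counts.**
- First group: (143 − 127)/143 = 16/143 = 11.2%.
- Second group: (123 − 97)/123 = 26/123 = 21.1%.
- Pooled proportion: 42/266 = 0.158. z = (0.2114 − 0.1119) / √[0.158 × 0.842 × (1/143 + 1/123)] = 2.22; chi-square = 4.92, p = 0.027 (0.040 with continuity correction; Fisher 0.029).
- With an assumed design effect of 1.5 for clustering, z = 2.22/√1.5 = 1.81, below 1.96.

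**3. If 220 is right, place the 4 extra losses.**

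| Extra losses, first / second group | First group | Second group | p |
|---|---|---|---|
| 0 / 4 | 16/143 = 11.2% | 30/123 = 24.4% | 0.005 |
| 1 / 3 | 17/143 = 11.9% | 29/123 = 23.6% | 0.012 |
| 2 / 2 | 18/143 = 12.6% | 28/123 = 22.8% | 0.029 |
| 3 / 1 | 19/143 = 13.3% | 27/123 = 22.0% | 0.062 |
| 4 / 0 | 20/143 = 14.0% | 26/123 = 21.1% | 0.124 |

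The gap is 7.2 to 13.2 points and its direction never changes.

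**4. The comparison that is on the list: arm.**
- Text counts: 46/266 = 17.3% versus 33/252 = 13.1%, p = 0.18.
- Caption counts: 42/266 = 15.8% versus 13.1%, p = 0.38.

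**5. Shift in stage mix among those retained.** The first group goes from 143/266 = 53.8% to 127/224 = 56.7%, a shift of 2.9 points. If progression differed by 50 points between stage groups (an assumption, and a large one), the arm's rate would move by 0.029 × 50 = about 1.5 points.

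**6. Would adding stage to an unstratified comparison be enough?** The documents give no control-arm loss by stage, so this step is an illustration only. Assume that the control arm has the same stage split (135/117) and vary how its 33 losses fall.

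| Assumed control losses, first / second | Unstratified comparison | p |
|---|---|---|
| 15 / 18 | 31/278 vs 44/240 | 0.021 |
| 18 / 15 | 34/278 vs 41/240 | 0.12 |
| 24 / 9 | 40/278 vs 35/240 | 0.95 |

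If control losses lean the same way, the unstratified test finds the difference. If they are unrelated to stage or lean the other way, it does not. Showing the comparison by arm removes that dependence.

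**7. What the two planned scenarios cover.** Assume progression in 110/220 versus 77/219 completers.
- Completers: (110/110)/(77/142), odds ratio 1.84.
- All lost fail: (110/156)/(77/175) = 1.60.
- All lost succeed: (156/110)/(110/142) = 1.83.
- Lost fail in the intervention arm and succeed in control: (110/156)/(110/142) = 0.91.

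The last case is an extreme, but it lies outside the range of the two planned scenarios because each gives the lost the same outcome in both arms.

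**The case against.** The best defence is that the plan does not rest on this check. The two scenario analyses follow directly, are unconditional, and are reported whatever the baseline comparison shows. Intervention-arm loss by stage group is already published in the Figure 2 caption, so nothing is hidden. Dietary behaviors might be read broadly enough to include stage. The text does not say that the tables will be unstratified. Details of attrition tables and missing-data models are commonly left to an analysis plan. And the shift in stage mix is small.

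Much of this stands. The scenario analyses are a real safeguard, the shift is modest, and the absence of a particular imputation or weighting model from an article is not a fault. Three things remain. Participant Timeline lists stage separately from dietary practices and intake, so the broad reading is doubtful. The article does fix a specific list and a specific purpose, and the list does not serve the purpose. And the scenarios treat the lost alike in both arms, so they do not cover loss that differs by arm.

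**Conclusion.** The point holds in a limited form. As written, the check could conclude that loss was not selective, because the listed arm comparison is non-significant (p = 0.18 or 0.38) while the unlisted stage comparison in the intervention arm is 11.2% versus 21.1% (p = 0.027). That p-value ignores clustering and depends on the caption's counts; with the 4 unreconciled participants it lies between 0.005 and 0.124. The direction is firm, the significance is not. The direct effect on stage mix is small.

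Three stronger readings are not supported.
- A reader might infer that the effect estimate is materially biased. The documents give no control-arm loss by stage, and the measured shift is 2.9 points.
- A reader might infer that stage caused the difference in loss. The caption does not say which stages form which group, and in this arm stage is tied to the type of intervention.
- A reader might infer that the lost participants of the higher-loss group failed to progress, so that its observed rate is inflated. Nothing shows their outcomes. Adding stage to the check would not reveal them, and the planned all-failure analysis already codes them that way.

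**What to change.** In Data Analysis:
- Add baseline stage group (precontemplation and contemplation versus preparation, action and maintenance) and baseline diet status to the compared characteristics.
- Present lost versus retained within each arm, control included, with loss by stage group.
- State the purpose as describing loss. A non-significant comparison with 79 of 518 lost (15.3%) cannot ensure its absence.
- Beside the two planned scenarios, add one sensitivity analysis that uses arm and baseline stage: multiple imputation or inverse-probability-of-retention weighting. It would address loss related to arm and stage, not loss that depends on the unseen outcome.

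In Results and the Figure 2 caption, reconcile 220 with 224 and say which stages form each group.

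The cost is a few tables and one model on data already collected; the article reports the effectiveness analysis as still to be completed. The downside is a little more analysis work, and the no-selective-loss statement may have to be dropped.

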## Results

As of December 2024, baseline data collection, participant enrollment, intervention administration, and postintervention data collection have been completed. Altogether, 610 workers from 20 offices were screened for eligibility. Of the 610 workers, 92 (15.1%) were excluded due to not meeting the eligibility criteria (n=12, 13%) and not consenting (n=80, 87%). A total of 518 participants were recruited for the baseline assessment, and then 20 offices were randomized to the control and intervention groups. The intervention group comprised 51.4% (266/518) of the participants, whereas the control group comprised 48.6% (252/518) of the participants. Ultimately, 439 participants (n=220, 50.1% in the intervention group and n=219, 49.9% in the control group) were included in the postintervention data collection. Figure 2 shows the CONSORT (Consolidated Standards of Reporting Trials) flowchart up to the completion of follow-up. Data analysis of the effectiveness of the intervention is to be completed and published. Data collected at baseline (before the intervention) were published as a descriptive study on dietary intake among office workers. However, none of the data related to the intervention have been published.

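### The two planned loss-to-follow-up analyses give lost participants the same outcome in both arms, so together they do not bound attrition bias

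*Protocol article*

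**What the plan says.** The Data Analysis section of the protocol article deals with loss to follow-up in two steps.

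- Background characteristics and allocated arm of "participants lost to follow-up will be compared with those of other participants to ensure no selective data loss".
- Two further analyses follow. In one, "all participants lost to follow-up achieved the primary and secondary outcomes". In the other, "all participants lost to follow-up did not achieve the primary and secondary outcomes". Neither assumption mentions arm. Reporting is fixed as well: "Odds ratios will be reported for the 2 assumptions separately".

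The Results section gives 266 intervention and 252 control participants at baseline. It then says: "Ultimately, 439 participants (n=220, 50.1% in the intervention group and n=219, 49.9% in the control group) were included in the postintervention data collection". The effectiveness analysis was still to be done when the article was written, so the plan can be changed.

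**The concern.** Loss to follow-up biases a comparison of arms when outcomes among the lost differ between arms in a way that the completers do not reveal. An example is intervention participants who disengage because they are not changing their diet, while control participants drop out for unrelated reasons. A sensitivity analysis for attrition should let the lost in one arm do better or worse than the lost in the other. Both planned scenarios hold the two equal, at 100% or at 0%.

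What is at stake is the robustness statement in the final report. Two similar odds ratios could be read as showing that attrition does not matter, although the harmful pattern was never tried. The wording "to ensure no selective data loss" points the same way. A comparison on measured characteristics cannot exclude selective loss on an outcome that was not observed.

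**Working it through.** **Inputs.** Baseline 266 and 252, follow-up 220 and 219 (Results). Assumed completer rates 0.45 and 0.30 (Sample Size). These are rates of recommended fruit and vegetable intake; the article gives none for progression in stage of change, the primary outcome. Intraclass correlation 0.02 (Sample Size).

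**The plan's own figures.** 266 + 252 = 518 and 220 + 219 = 439, as stated. The rates 0.30 and 0.45 reproduce the stated 160 per arm: (1.96 + 0.84)² × (0.30×0.70 + 0.45×0.55) / 0.15² = 159.6, at two-sided 5% (sidedness is not stated) and 80% power.

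**Loss.** Intervention 266 − 220 = 46 (17.3%). Control 252 − 219 = 33 (13.1%). Overall 79/518 = 15.3%, against 10% allowed for in the sample size.

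**General form.** Let a and b be the success rates among the lost in the intervention and control arms. With 0.45×220 = 99 and 0.30×219 = 65.7 successes among completers:

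RD = (99 + 46a)/266 − (65.7 + 33b)/252 = 0.111 + 0.173a − 0.131b

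The planned analyses are the points a = b = 1 and a = b = 0. They differ by 17.3 − 13.1 = 4.2 points. Over all a and b, RD spans 17.3 + 13.1 = 30.4 points. Neither width depends on the completer rates.

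| Assumption about the lost | Intervention | Control | RD (points) | OR |
|---|---|---|---|---|
| Completers only | 99/220 = 45.0% | 65.7/219 = 30.0% | +15.0 | 1.91 |
| All succeed (planned) | 145/266 = 54.5% | 98.7/252 = 39.2% | +15.3 | 1.86 |
| All fail (planned) | 99/266 = 37.2% | 65.7/252 = 26.1% | +11.1 | 1.68 |
| Intervention fail, control succeed | 37.2% | 39.2% | −1.9 | 0.92 |
| Intervention succeed, control fail | 54.5% | 26.1% | +28.4 | 3.40 |

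**Tests.** Wald test on the log odds ratio, control successes rounded to 66, variance inflated by 1 + (518/20 − 1)×0.02 = 1.50. All succeed gives p = 0.005 and all fail gives p = 0.028, so both planned analyses keep the conclusion. Intervention fail with control succeed gives p = 0.69.

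**A less extreme case.** Take b = 0.30, the control completer rate, and a = 0.10. Intervention is (99 + 4.6)/266 = 103.6/266 and control 75.6/252, so OR = (103.6/162.4)/(75.6/176.4) = 1.49, with p = 0.08 after the same inflation. With a = 0 the OR is 1.38 and p = 0.16. Neither planned scenario comes near this pattern.

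**How far the estimate must move to vanish.** With a = 0, RD reaches zero at b = 0.111/0.131 = 0.85. Losing significance takes much less.

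**Alternative count.** The Figure 2 caption gives 127 + 97 = 224 intervention participants at the end, not 220. Then 42/266 = 15.8% were lost, the range is 15.8 + 13.1 = 28.9 points, and the worst case is 100.8/266 − 98.7/252 = −1.3 points. The conclusion is the same.

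**The case against.** **The planned pair is not empty.** A reader might infer that it can hardly change any conclusion, or will look reassuring whatever the true bias. The figures do not support that. With completers at 40% against 30%, p = 0.031 (ignoring clustering) becomes 0.087 under all-fail. With the 1.50 inflation, p = 0.078 becomes 0.039 under all-succeed. At 42% against 30% with inflation, 0.038 becomes 0.091 under all-fail. On an unweighted grid of significant favourable completer results with differences up to 20 points, all-fail removed significance in 31% (unclustered) to 39% (inflated). This objection stands.

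**The pair does not lean one way.** All-succeed raises the arm that lost more, so with 30% success in both arms it gives an odds ratio of 1.13. All-fail gives 0.94 on the same inputs. Both are to be reported, so a charge of bias towards the intervention would be unfair.

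**Differential loss is not established.** 46/266 against 33/252 gives Fisher p = 0.22, ignoring clustering, which is compatible with chance. Within the intervention arm the caption shows 16/143 (11.2%) and 26/123 (21.1%) lost in the two stage-based groups, and a reader might infer stage-dependent loss from p = 0.03. Those counts imply 224 followed up, against 220 in the text. Depending on where the other four losses belong, p runs from 0.006 to 0.14. The point needs neither comparison, because outcomes among the lost can differ by arm even when loss is equal.

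**The scenarios are supplementary.** The article presents them as further analyses after the main ones, and ranking sensitivity analyses can be left to an analysis plan that is not shown. That is fair, so the absence of a statement on which result governs is no finding. But the article itself fixes the two scenarios, and neither allows the arms to differ.

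**Conclusion.** The point holds in this form: the two planned analyses do not bound attrition bias. They cover 4.2 of the 30.4 risk-difference points that the missing outcomes allow (28.9 if 224 were followed up). These widths rest only on the published counts.

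The odds ratios rest on the assumed 45% and 30% in completers, which are not rates for the primary outcome. At those rates the planned pair (1.86 and 1.68) leaves the conclusion unchanged, while the opposed extremes run from 0.92 to 3.40. It does not follow that the trial's result is biased, that loss was selective, or that the planned analyses are useless. What follows is that agreement between them would not show robustness to attrition. This is a worthwhile, cheap improvement and not a fatal flaw.

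**What to change.** 1. Keep the two planned scenarios.
2. Add a tipping-point analysis for each outcome that varies the success rate among the lost from 0 to 1 separately in each arm, with the two opposite-direction extremes as end points. Report where the estimate and the conclusion change. The grid matters more than its corners: the worst corner removed significance from every result on the grid described above, so on its own it discriminates poorly.
3. Base any statement of robustness to attrition on this analysis.
4. Replace "to ensure no selective data loss" with wording that says the comparison describes the losses.
5. Reconcile the 220 in the Results text with the 224 implied by the Figure 2 caption before fixing the number lost.

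Cost: a few hours of analysis, a few revised sentences and no new data. The downside is that the robustness statement may turn out less favourable.
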